## Abstract

**Abstract::**

**Introduction:**

Severe perinatal asphyxia at term or near term remains a critical public health issue, associated with high risks of neonatal death and hypoxic-ischaemic encephalopathy (HIE). Despite improved clinical guidelines, suboptimal care persists in many cases, and previous audits have demonstrated that up to 50% of asphyxia cases could be associated with suboptimal care. OptiNeoCare is a French study which aims to assess the prevalence and determinants of suboptimal obstetric and neonatal care and evaluate its potential impact on neonatal outcomes.

**Materials and methods:**

This prospective, population-based observational study will include newborns ≥36 weeks’ gestation with severe perinatal asphyxia across 12 French perinatal networks (213 maternity units). Inclusion criteria comprise neonatal death or moderate/severe HIE with confirmed biochemical markers of asphyxia. Data will be collected prospectively from labour wards, transport teams and neonatal intensive care units using an electronic case report form, and the in-situ team will be invited to complete a morbi-mortality review (MMR). Approximately 336 cases will be included over 12 months, with 25% randomly selected for confidential enquiry by two experts. The quality of care will be assessed based on a structured classification of medical errors (diagnostic, therapeutic, preventive and systemic) by a panel of experts including an obstetrician or midwife and a paediatrician. Root cause analysis will identify determinants of suboptimal care. A concordance analysis will compare findings from MMRs and confidential enquiries. Statistical analysis will include multivariable logistic regression to explore associations between care quality and neonatal outcomes.

**Ethics and dissemination:**

Ethical approval was granted by the Ethics Committee for Research in Obstetrics and Gynaecology. Informed non-opposition is required from participants. Results will be shared with participating centres, healthcare professionals and through scientific dissemination.

**Trial registration number:**

ClinicalTrials.gov ID: NCT06322732.

STRENGTHS AND LIMITATIONS OF THIS STUDYThis study will focus on severe perinatal asphyxia, a critical yet rare condition with high morbidity and mortality, to evaluate the quality of care and identify opportunities for improving neonatal outcomes.This study will be a population-based multicentre study involving 213 maternity units across 7 French regions, ensuring comprehensive national coverage and generalisability of findings.Prospective and detailed data collection on obstetric, neonatal, transport and organisational factors will allow for indepth analysis of care pathways.The methods will associate an in-situ morbi-mortality review and a standardised expert review process using a confidential enquiry methodology to assess the quality of perinatal care.A perinatal study combining obstetric, neonatal and transport data collection through structured questionnaires.

## Introduction

 Perinatal asphyxia at term is a severe condition that can result in peripartum death or a birth with critical distress, leading to neurological impairment known as hypoxic-ischaemic encephalopathy (HIE), which occurs in approximately 1.6 per 1000 births.^1^ As an unexpected and urgent situation, obstetric and neonatal management plays a crucial role in determining neonatal and neurological outcomes.^2^ Despite significant improvements in prognosis over recent years,^3^ the condition remains severe, with an estimated mortality rate of 15–20% and a risk of moderate to severe disability in 30% of survivors.^4^

The management of severe perinatal asphyxia involves multiple risk factors that have been identified as contributors to suboptimal care in this particularly vulnerable patient population. Batlle *et al*’s clinical audit of obstetric practice in France in 2010, conducted through peer review, revealed that half of the audited cases of peripartum asphyxia were deemed ‘possibly or certainly avoidable’.^5^ Similar findings have been reported in studies from Denmark and Sweden.^6 7^ Additionally, Chevallier *et al*^8^ in France demonstrated that approximately 35% of neonates requiring therapeutic hypothermia did not receive it in accordance with national guidelines.^9^ The analysis of these suboptimal care practices aims to identify systemic factors leading to errors and to propose solutions to prevent similar cases in the future.^10^

Corrective actions have been implemented based on these studies. ‘Each Case of Asphyxia Could Be Used as a Learning Example’ is the title of an article proposing clinical practice recommendations derived from perinatal asphyxia case audits.^11^ In Queensland, the implementation of a national fetal heart rate monitoring education programme significantly reduced the incidence of HIE from 250 to 160 events per 100 000 live births.^12^ In the UK, a pragmatic approach has been initiated to improve outcomes in perinatal asphyxia. *Each Baby Counts* (https://www.rcog.org.uk/eachbabycounts) is a national platform that records all cases of perinatal asphyxia and HIE while collecting data on suboptimal care practices. This initiative aims to enhance care quality both locally and nationally.

These experiences suggest that the identification of suboptimal obstetric and neonatal care through voluntary institutional engagement can improve prevention and management. In France, the analysis of severe adverse events is conducted through morbidity and mortality reviews (MMR), which remain internal to healthcare institutions and have a limited national impact. However, the prevalence, causes and risk factors—whether individual or related to healthcare organisation—as well as the evaluation of suboptimal care at a population level, have not been systematically assessed. The confidential enquiry remains the gold standard for identifying suboptimal care. However, to date, no study has directly compared this method with routine in-situ MMRs in neonates.

The aim of this study is to describe cases of perinatal death or HIE, analyse associated risk factors and evaluate the quality of obstetric and neonatal care.

## Methods and analysis

OptiNeoCare is a prospective population-based observational study with an assessment of the optimality of the obstetric and neonatal care pathway.

### Data analysis plan

The first inclusions are expected to begin in May 2025. Four expert panel meetings will be held at regular intervals to assess the quality of care through confidential enquiries, conducted between the third quarter of 2025 and the third quarter of 2026. Data analysis will begin in the fourth quarter of 2026, with results expected to be disseminated by the end of 2027.

### Design

All included cases will be assessed through an in-situ review using a standardised online questionnaire, completed by the designated referent from each maternity unit. These digital records will be analysed, compiled and summarised by the *OptiNeoCare* steering committee. For cases undergoing a local MMR, detailed information regarding the optimality of care will be documented and analysed.

For cases randomised for the confidential enquiry, two external assessors (one paediatrician and one obstetrician or midwife) will conduct an on-site review. The results of the assessment will then be entered directly into Cleanweb for each mother-newborn pair. The identification of suboptimal care and the determination of case preventability will be discussed by an expert panel. This evaluation will be based on recognised criteria (clinical guidelines, consensus statements, best practice recommendations or expert opinion in the absence of literature).

### Setting

This is a population-based study conducted across seven regions of France, involving 12 perinatal networks and a total of 213 maternity units: 32 level-3, 108 level-2, 69 level-1 units and four midwifery-led birth centres. These facilities contributed to the inclusion of 336 patients. Among the 213 participating maternity units, 44 are located in the Île-de-France region (including the city of Paris) and 169 in other regions: Pays de la Loire, Auvergne-Rhône-Alpes, Hauts-de-France, Bourgogne, Occitanie and Normandie. Each unit is affiliated with its respective perinatal referral centre.

### Patient and public involvement

All parents will be informed about the study through public notices (posters displayed in maternity wards and neonatal units) and via an individual information leaflet provided at admission, indicating that a study on the quality of care surrounding perinatal asphyxia is currently being conducted in the maternity unit where they will deliver.

The aggregated results of the survey will be presented at medical conferences that include parent committees, such as the SOS Prema and Hospitalized Babies Association, which participates in the French Society of Neonatology congress and The European Foundation for the Care of Newborn Infants, which is involved in organising European congresses. This will facilitate communication of the results to stakeholders. Additionally, the findings will be shared with the general public through information networks such as mainstream newspapers and other media outlets.

### Study population

The study population will include term or near-term newborns (≥36 weeks of gestation) presumed to be alive at the onset of labour and who presented with severe perinatal asphyxia, defined by both of the following criteria:

Clinical severity of neonatal outcome. At least one of the following criteria had to be met:Neonatal death during the initial hospital stay (from birth until discharge or before day 28 of life, whichever came first) or moderate to severe HIE or hospitalisation within the first week of life due to HIE or seizures attributable to a peripartum event.Biological evidence of perinatal asphyxia. At least one of the following:Arterial (or, if not available, venous) cord blood pH ≤7.10 or base deficit ≥16 mmol/L or lactate ≥11 mmol/L within the first 3 hours of life or in the absence of biochemical documentation of metabolic acidosis, one of the following criteria: Apgar score ≤5 at 5 min of life or need for neonatal resuscitation, defined as ventilatory support at birth and Apgar score ≤7 at 10 min. If no biochemical or Apgar data were available in the medical record (eg, in cases of home births): inclusion will be based on neonatal outcome (death, HIE or neonatal seizures).

Moderate or severe HIE is defined according to the criteria of the French Society of Neonatology, in the context of perinatal asphyxia, as follows: signs of cortical dysfunction: lethargy with diminished response to stimulation or coma with absent response; and at least one of the following: abnormal muscle tone, abnormal primitive reflexes, weak or absent sucking reflex, clinical seizures.

Peripartum event is defined as a sentinel event, such as uterine rupture, maternal haemorrhage or collapse, shoulder dystocia, meconium aspiration or cord prolapse; or abnormal fetal heart rate patterns during labour.

Exclusion criteria: intrauterine fetal death prior to hospital admission; termination of pregnancy for medical reasons; severe congenital anomalies that could potentially affect neonatal survival or long-term neurodevelopmental outcomes and neonatal encephalopathy not related to hypoxic-ischaemic origin.

### Primary outcome measure

The primary outcome will be the frequency of optimal versus suboptimal care observed during maternal and neonatal management in cases of moderate to severe HIE or neonatal death related to severe perinatal asphyxia.

Suboptimal care will be classified based on data entered in the electronic case report form (eCRF), using the framework described by Leape *et al*,^13^ encompassing the following categories:

Diagnostic errors (errors or delays in diagnosis; failure to perform indicated diagnostic tests; use of outdated diagnostic methods; misinterpretation of diagnostic test results).Therapeutic errors (errors in procedural performance; errors in medication administration; dosage errors; avoidable delays in treatment or in responding to abnormal test results; provision of inappropriate care).Preventive failures (lack of indicated prophylactic treatment; inadequate monitoring or follow-up of treatment).Other systemic or organisational failures (communication failures; equipment deficiencies; other system-level failures).

### Secondary outcomes

#### Neonatal outcome

Neonatal outcome will be defined using a composite endpoint that includes both mortality (early neonatal death within the first 24 hours of life or during the initial hospitalisation prior to any potential discharge home) and/or severe neonatal morbidity (defined as the presence of brain lesions on MRI attributable to perinatal asphyxia according to the NICHD classification)^14^ and/or an abnormal electroencephalogram performed within the first week of life according to the classification of Lamblin *et al*^15^ and/or clinical abnormalities assessed using the adapted Sarnat classification at birth^16^ and subsequently using the Amiel-Tison neurological assessment during the first week of life.^17^

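### On its literal and/or wording, the composite neonatal outcome largely restates the entry criteria, which would leave few non-events for the planned regression on care quality

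*Protocol article*

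**What the plan says.** **Entry (Study population).** Besides evidence of asphyxia, an infant must meet one clinical criterion: "Neonatal death during the initial hospital stay", or "moderate to severe HIE or hospitalisation within the first week of life due to HIE or seizures attributable to a peripartum event". Moderate or severe HIE is itself defined by neurological signs: "signs of cortical dysfunction: lethargy with diminished response to stimulation or coma with absent response", plus at least one of abnormal tone, abnormal primitive reflexes, poor or absent suck, or clinical seizures.

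**Outcome (Secondary outcomes, Neonatal outcome).** The composite joins four elements by and/or: death in the first 24 hours or the initial stay; MRI lesions attributable to asphyxia (NICHD classification); an abnormal EEG in the first week; and "clinical abnormalities assessed using the adapted Sarnat classification at birth", then the Amiel-Tison assessment during the first week. The article states no grade above which the EEG or the clinical element counts.

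**Analysis.** The abstract says: "Statistical analysis will include multivariable logistic regression to explore associations between care quality and neonatal outcomes". The Statistical methods section applies the primary outcome's model type, logistic regression, to the secondary outcomes. The abstract's stated purpose, after measuring suboptimal care, is to "evaluate its potential impact on neonatal outcomes".

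**The concern.** A logistic model for a binary outcome needs a reasonable number of infants on each side. Here the list that admits an infant and the list that counts as a bad outcome overlap heavily. If nearly every infant is an event, the odds ratio for care quality depends on the few who are not, and adjustment for several covariates is out of reach.

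Two related points follow:

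- Sarnat status at birth precedes the transport and intensive-care phases on which the study also collects data, so that component cannot respond to the quality of that later care.
- Every infant is selected on outcome. The regression can therefore compare severity among cases, but it cannot show whether care changed the chance of injury occurring.

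**Working it through.** **1. The plan's own figures.** From Sample size: 340 000 births × 1/1000 = 340, against 336 stated (1.2% apart). 336 × 0.25 = 84 enquiry cases. Suboptimal care is assumed in 50%. No event rate, effect size or power is stated for the neonatal-outcome regression, so there is no figure of that kind to reproduce.

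**2. Entry routes set against the composite.**

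| Entry route | Composite element met | Met by definition? |
|---|---|---|
| Neonatal death in the initial stay | Mortality | Yes |
| Moderate or severe HIE | Clinical abnormality: the entry signs are of the kind the Sarnat element records | Yes, on the literal reading |
| First-week admission for HIE or seizures | Clinical or EEG abnormality, no grade stated | No, but usually |

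**3. Non-events and power.** Assumptions, none of them in the article: non-event share s, half of the infants exposed to suboptimal care (in line with the plan's 50%), two-sided alpha 0.05, true odds ratio (OR) 2 or 3, no covariates.

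- Non-events = N × s.
- Let a and b be the non-event proportions under optimal and suboptimal care, with (a + b)/2 = s and odds(b) = odds(a)/OR.
- With n = N/2 per group, power = Φ{[(a − b) − 1.96·√(2s(1 − s)/n)] / √([a(1 − a) + b(1 − b)]/n)}.
- Example: s = 0.10, OR 2, N = 336 gives a = 0.1303 and b = 0.0697. With n = 168, the numerator is 0.0606 − 1.96 × 0.0327 = −0.0036, the denominator is 0.0326, and power is about 0.46.

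| Assumed non-event share | Non-events of 336 | Power, OR 2 | Power, OR 3 | Non-events of 84 | Power, OR 2 (N = 84) |
|---|---|---|---|---|---|
| 1% | 3 | 0.09 | 0.15 | 1 | 0.05 |
| 2% | 7 | 0.14 | 0.25 | 2 | 0.06 |
| 5% | 17 | 0.27 | 0.53 | 4 | 0.10 |
| 10% | 34 | 0.46 | 0.81 | 8 | 0.15 |
| 20% | 67 | 0.70 | 0.97 | 17 | 0.24 |

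At ten non-events per model parameter, the rows for 336 infants support 0, 0, 1, 3 and 6 parameters. The normal approximation is rough in the top rows, so those powers are indicative only. The 20% row is shown for a more generous reading of the definition.

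**4. An outcome that does not saturate, for comparison.** The Introduction gives mortality of 15–20%, so death alone yields 336 × 0.15 = 50 to 336 × 0.20 = 67 events. The article gives no MRI lesion rate; assume 30–50% of survivors. Death or MRI injury is then 0.15 + 0.85 × 0.30 = 40.5% to 0.20 + 0.80 × 0.50 = 60%, or about 136 to 202 events of 336. Power for OR 2 is about 0.87 at either end.

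**The case against.** **The rate is unknown.** The article gives no composite event rate. A reader might infer that virtually 100% of infants are events and that the odds ratio cannot be estimated. The document does not establish that. At a 10% non-event share, power for OR 3 is 0.81, and at 20% it is 0.97. This stands: the size of the problem is a range that rests on an assumption.

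**The clinical element may require persistence.** The wording runs from Sarnat at birth to a later Amiel-Tison examination. If abnormality must still be present at the later one, infants who recover within the week with normal MRI and EEG become non-events, and the contrast improves. The reading is possible, but the text does not state it.

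**Grades may be set elsewhere.** The EEG, MRI and Sarnat elements refer to published classifications, and a fuller document may fix cut-offs. That is fair for the EEG element. It does not remove the overlap of the death and HIE routes, which comes from the and/or structure the article itself states.

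**Overlap alone is not the test.** EEG abnormality is not an entry criterion, though one could be misled into treating it as one; it overlaps only through HIE and seizures. Death is an entry criterion and yet a sensible outcome, because it varies among cases. What matters is whether the combined outcome still separates infants.

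**The aim is modestly worded.** A reader might infer that the study claims to estimate a causal effect on whether injury occurs. The abstract speaks only of potential impact and of exploring associations, the Introduction's closing aim is descriptive, and avoidability is judged separately by experts. A case-only sample is the declared design. What remains is a wording point.

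**Conclusion.** The point holds for the definition as written. Two of the three entry routes meet the composite by definition and the third usually will, so the logistic regression on care quality would have few non-events. Under an assumed 1–10% non-event share there are about 3 to 34 non-events of 336, with power of about 0.09 to 0.46 for OR 2, and about 1 to 8 non-events among the 84 enquiry cases. A persistence requirement for the clinical element would enlarge the non-event share, but the article does not state one.

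A few non-events could also come from intrapartum stillbirths, which Sample size counts but which are not literally neonatal deaths. A contrast that coded them as favourable outcomes would mislead.

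It would be wrong to conclude that the study's main result is at risk. The frequency of suboptimal care, its types and determinants, avoidability, and concordance between local review and enquiry do not depend on this composite, nor does the sample size. The defect lies in one exploratory secondary outcome and is worth correcting before analysis.

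**What to change.** - Drop Sarnat status at birth from the composite, because it duplicates entry.
- Define the neonatal outcome by severity beyond entry: for example, death or asphyxia-related MRI injury on the NICHD classification, or an ordinal scale of no lesion, graded MRI injury and death, analysed with an ordinal model. Death stays as the most severe level.
- Report EEG and the first-week examination as separate outcomes, or include them only above a stated grade. If persistence to the first-week examination is intended, say so.
- State how intrapartum stillbirths are classified in this outcome.
- Describe the result as an association of care quality with severity among cases, not as an impact on whether injury occurs.

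The cost is the redefinition of one secondary outcome and a few words in the aim; MRI, EEG and examination are already elements of the planned outcome. The downside is that EEG and clinical findings become separate outcomes. Even after the change, the 84 enquiry cases alone give power of only about 0.34 for OR 2 at the 40.5–60% event rates above, so results in that subset should be presented as descriptive. The change should be made before analysis begins, which the article places in the fourth quarter of 2026.

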#### Characteristics of suboptimal care identified by expert reviewers

Suboptimal care will be analysed using the medical error classification proposed by Leape *et al*^18^ (as described in the primary outcome) with attention to characteristics indicative of systemic errors.

#### Determinants of suboptimal care

Determinants will be explored using a root cause analysis (RCA) approach. RCA focuses on identifying the initiating factor(s) that triggered the chain of events leading to patient harm. The aim is to highlight systemic factors contributing to the error,^10^ such as level of maternity unit, timing of care (eg, during night shifts), staff qualifications, equipment used, etc.

#### Assessment of the potentially avoidable nature of the case

Suboptimal care with a potentially avoidable complication refers to an event that could have been avoided through appropriate error management strategies.^19^ The assessment of avoidability includes a subjective component and will be determined by expert consensus based on the optimality of care provided. In the absence of consensus, inter-rater agreement will be measured using Cohen’s Kappa coefficient, with values >0.61 considered sufficient for this study. Cases will be classified into three categories: probably avoidable, probably unavoidable or undetermined.

#### Concordance between data collected in the eCRF and local MMR review versus confidential enquiry findings

This analysis will be both qualitative and quantitative, comparing the data reported in the eCRF completed by the referring clinician and the local MMR with the findings from the national-level confidential enquiry.

### Study organisation

All parents will be informed of the study through public notices (posters displayed in maternity wards and neonatal units) and via an individual information leaflet provided at admission. The designated clinician (obstetrician, neonatologist or midwife) will record in the medical file the absence of opposition from the mother to the collection of her personal data, as well as the absence of opposition from both parents regarding the collection of data concerning their newborn (figure 1).

